### Follow up

Participants will complete a follow-up assessment at 3, 6, and 12 months. Follow-up assessments will be conducted electronically. Participants who do not complete the follow-up assessment 3 days after having received the email providing the link to the questionnaire will be sent a first reminder by email. A second reminder will be sent 3 days later. In the case of non-response after two reminders, participants will be contacted by research assistants over the phone (up to five unanswered calls) and by text message (up to three messages). Research assistants will encourage participants to complete the questionnaire online. Once the questionnaire is complete, participants will receive an incentive. Incentives will be electronic coupons (up to 50 Swiss francs (CHF) if all assessments/tasks are completed). This strategy has been used successfully in a previous study with electronic follow up conducted by our group and allowed a high follow-up rate (91% at 6 months among people with unhealthy alcohol use) [5, 6].

### Data collection

All assessments will be conducted electronically and recorded directly on a secure electronic case report form that is independently managed, to ensure data integrity, security, quality, and traceability. The electronic forms will be tested before the study to ensure the quality of data recording. The final trial dataset will be accessible to investigators at the end of the study. Data will be publicly available after publication of the trial results.

### Statistical analyses

The primary analysis will answer the main research question: “Is providing access to a smartphone app effective in reducing drinking compared to a no-intervention control condition?” The primary analysis will be to compare the intervention and control groups at 6 months on the primary outcome measure: the volume of alcohol drunk reported as the mean number of drinks per week over the past 30 days. All available data will be used in an intent-to-treat paradigm (i.e. individuals will be analyzed according to their initial group allocation). Missing values will be handled through a multiple imputation procedure in order to respect the intention-to-treat paradigm [28]. The null hypothesis is that both conditions have comparable effects on the volume of drinking at the 6-month follow up. The alternative hypothesis is that participants in the intervention group (experimental condition: secondary prevention intervention) will report a smaller volume of drinking at the 6-month follow up compared to participants in the control group.

Count models will be used. Because we are expecting that the data will not be normally distributed, an adequate count model will be selected by comparing different count models. From previous studies conducted with the same outcome, we expect a negative binomial regression model to best fit the distribution of the sample [5, 6]. If this is confirmed, the impact of the intervention will be assessed by a random-effects negative binomial model for mean number of drinks per week. The model will specify subject and recruitment site as random effects and intervention and time as fixed effects (with a time * intervention interaction term). The model will be adjusted for age and gender.

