### Outcome measures

The primary outcome will be self-reported volume of alcohol drunk over the past 30 days, reported as the mean number of standard drinks per week over the past 30 days, measured at 6 months. This will be assessed with a validated quantity/frequency measure [48]. It has been demonstrated that electronic self-report of alcohol use is valid and that social desirability bias is limited [15]. Compared to a drinking diary, which is more burdensome to participants, this type of measure has been shown to limit attrition and to be functionally identical to drinking diary methods [17, 54].

Secondary outcomes will be the number of heavy drinking days (i.e. days with five drinks or more consumed by men or four drinks or more by women) over the past 30 days, at 6 months. Additional outcomes will be the maximum number of drinks on any day over the past 30 days, alcohol-related consequences (measured using the Short Inventory of Problems (SIP-2R) [33], and academic performance. Academic performance will be assessed by the following question: “How do you rate your performance in comparison with your fellow students?” (with response options: much worse, worse, similar, better, much better).

These outcomes will be used for the main analysis (primary hypothesis: providing access to the app will be associated with changes in drinking outcomes) and for the per-protocol analysis (secondary hypothesis: accessing the app will be associated with changes in drinking outcomes).

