#### Secondary outcomes

The same procedure will be applied to secondary outcomes: number of heavy drinking days, maximum number of drinks on any day, SIP-2R score, and academic performance score.

In order to test the secondary hypothesis that participants who used a smartphone app targeting unhealthy alcohol use will have greater reductions in drinking compared to the no-intervention control condition, the analyses will be replicated in the subsample of participants who actively downloaded the application or completed the matching procedure in the control group. Thus, participants randomized to have access to the app and who will actively use it will be compared to those randomized to the no-intervention control condition who completed the matching procedure (entering a personalized code on a website). This analysis is equivalent to a per-protocol analysis.

Analyses will be performed at the completion of data collection. Subgroup analyses will be performed among participants reporting a high level of drinking and potential alcohol use disorder. In order to examine the potential for differences in the efficacy of the application among these participants, we will conduct secondary analyses in subgroups: in men we will conduct secondary analyses among those with baseline AUDIT score > 10 and AUDIT scores > 13 [23]: in women the cut-off points will be AUDIT scores > 6 (optimal sensitivity/specificity for *Diagnostic and statistical manual of mental disorders* (DSM-5) alcohol use disorder) and AUDIT scores > 11) [23].

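### The primary model is chosen by its fit to the trial data and the effect measure is not fixed independently of that choice, so a zero-inflated or hurdle model could change what the primary test estimates

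*Protocol article*

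**What the plan says.** The Outcome measures section of the protocol article defines the primary outcome as "the mean number of standard drinks per week over the past 30 days", measured at 6 months. The Statistical analyses section sets the comparison: "The primary analysis will be to compare the intervention and control groups at 6 months on the primary outcome measure". Its alternative hypothesis is that the intervention group "will report a smaller volume of drinking at the 6-month follow up compared to participants in the control group". Both concern total volume in everyone randomized.

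The same section leaves the model open. It states that "an adequate count model will be selected by comparing different count models", and then, citing earlier studies, that "we expect a negative binomial regression model to best fit the distribution of the sample". The consequence is conditional: "If this is confirmed, the impact of the intervention will be assessed by a random-effects negative binomial model for mean number of drinks per week". Its terms are given: random effects for participant and site; fixed effects for arm, time and their interaction; adjustment for age and gender. The article does not say which model follows if the negative binomial is not confirmed, or which effect measure would then carry the primary test.

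Under Secondary outcomes, "The same procedure will be applied to secondary outcomes", and the list that follows includes heavy drinking days and maximum drinks on any day.

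**The concern.** A negative binomial model with its usual log link gives one treatment effect per time point, the ratio of mean drinks per week between arms. That matches the stated comparison. A zero-inflated or hurdle model gives two: one for belonging to the zero group and one for volume among the rest. Neither alone is the stated comparison. A student who stops drinking because of the app counts as a success under the stated alternative hypothesis, yet mostly drops out of the volume coefficient.

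The choice rests on the trial's own outcome distribution. If that distribution has excess zeros, a fit comparison would tend to favour such a model, and the plan does not say that the mean contrast must still be the one reported. What is at stake is the meaning of the primary result: a real fall in overall drinking could be missed, or a difference reported where overall means are equal. The same holds for the secondary counts. Heavy drinking days in particular may well have many zeros.

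**Working it through.** **Arm size.** The Sample size section gives 551 per group before inflation, then 771, then 771 + 77 = 848. The 771 is reproduced with an intraclass correlation of 0.001 and an assumed 400 participants per site: 551 × (1 + 399 × 0.001) = 551 × 1.399 = 770.8. The simulations use 771 per arm, or 848 × 0.9 ≈ 763 completers. No sample-size figure changes because of this point.

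**Algebra.** Let π be the share of structural zeros and μ the mean among the rest. Then E[Y] = (1 − π)μ, and

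overall mean ratio = [(1 − π₁)/(1 − π₀)] × (μ₁/μ₀).

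The volume coefficient estimates only μ₁/μ₀. The two agree when π₁ = π₀.

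**Inputs that are assumptions.** The article gives no mean, dispersion or share of zeros. Simulation A assumes a control mean of 8 among participants who are not structural zeros, dispersion 0.6 (0.8 in the last row), 771 per arm, the 6-month time point only, 300 runs per row, and model-based standard errors. NB is the negative binomial and ZINB its zero-inflated form, with treatment in both parts.

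| Zeros, control / app | μ₁/μ₀ | Overall mean ratio | NB mean ratio significant | ZINB volume part significant | AIC picks ZINB |
|---|---|---|---|---|---|
| 10% / 10% | 1.0 | 1.00 | 3.7% | 5.3% | 100% |
| 10% / 20% | 1.0 | 0.80/0.90 = 0.889 | 54% | 4% | 100% |
| 10% / 15% | 0.9 | (0.85/0.90) × 0.9 = 0.85 | 87% | 56% | 100% |
| 10% / 18.2% | 1.1 | (0.8182/0.90) × 1.1 = 1.00 | 3.3% | 50% | 100% |
| 0% / 0% | 0.87 | 0.87 | 77% | 76% | 5% |

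The Monte Carlo standard error is √(0.05 × 0.95/300) = 1.3 points near 5% and √(0.5 × 0.5/300) = 2.9 points near 50%.

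**Second set of assumptions (simulation B).** 763 per arm, mean 36 drinks per 30 days (36 × 7/30 = 8.4 per week), dispersion 0.8. With zeros of 5% against 13% and a volume ratio of 0.95, the overall ratio is (0.87/0.95) × 0.95 = 0.87. The mean ratio is significant in about 75% of runs and the volume part in 17% to 21%. With zeros of 10% against 18.2% and a volume ratio of 1.1, so that overall means are about equal, the volume part is significant in about 45%. With no excess zeros, the zero-inflated model is chosen in 0% to 3% of runs and the two analyses agree.

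**Reading.** Row 1 shows no inflation of type I error when both parts are null. Rows 2 and 3 show an overall reduction that the volume coefficient picks up less often or not at all. In row 4 the volume coefficient correctly detects a ratio of 1.1 among the rest, so it is not a false positive for its own hypothesis. It answers a different question from the one stated. Row 5 shows that without excess zeros nothing is lost.

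**The case against.** The article never mentions a zero-inflated, hurdle or other two-part model. It names the negative binomial, gives a reason for expecting it, and lists the model terms. A Poisson or quasi-Poisson alternative would keep the same mean ratio, and a zero-inflated model can still yield the marginal mean contrast if it is derived. The harm therefore needs three things together: excess zeros, choice of a two-part model, and its volume coefficient reported as primary. Participants are selected on a positive AUDIT-C, so zeros may be few. The list of candidate models, the fit criterion and whether selection is blind to arm are details that a condensed article commonly leaves to an analysis plan.

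All of this stands, and it limits the point. What remains is a rule that the article does state: the model depends on fit to the trial sample, with no effect measure tied to the fixed question.

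A reader might infer more than the documents support:

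- *That the plan will replace the mean ratio with a two-part model.* Nothing says so; it is only not excluded.
- *That choosing the model on the data inflates type I error.* The volume part alone rejects in 5.3% under the null. In simulation B on weekly values, counting either part as a success gives 4.4% and 4.9% at 3% and 5% zeros. Higher figures (9.3% on weekly values at 10% zeros, 7% to 11% on 30-day totals) arise only under that either-part rule, which the article does not propose.
- *That power is lost under any reading of a two-part model.* Under the either-part rule, power in simulation B is 86% to 100%. The low figures belong to the volume coefficient alone.
- *That rounding weekly values distorts the selection.* The article proposes no rounding.

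The high selection rates for the zero-inflated model are also partly built in, because structural zeros were simulated. The simulations use one time point, without the planned random effects, repeated measures or imputation.

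**Conclusion.** The point holds in a conditional form. The protocol article makes "a random-effects negative binomial model for mean number of drinks per week" depend on fit to the trial's outcome data and does not fix the effect measure apart from the model. If excess zeros lead to a zero-inflated or hurdle model and its volume coefficient becomes the primary result, the test leaves the stated comparison of mean drinks per week at 6 months in all randomized participants.

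Under the assumed inputs the effect can be large in either direction: 4% against 54% significant when the overall mean falls by 11%, and 50% significant when overall means are equal. With no excess zeros, or with a Poisson-type alternative, the effect measure is unchanged. The sizes show the mechanism and do not predict this trial, because the article gives no mean, dispersion or share of zeros. This is a cheap improvement rather than a flaw that undermines the trial. An analysis plan that already fixes the effect measure would settle it.

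**What to change.** - State that the primary effect measure is the 6-month intervention/control ratio of mean drinks per week in all randomized participants, whatever model is used.
- Prespecify the log-link negative binomial model, with the random effects, fixed effects, interaction and covariates already listed, as the primary analysis with robust standard errors.
- Keep other count models, zero-inflated ones included, as labelled sensitivity analyses.
- If a selection step is kept, carry it out on pooled, arm-blinded data and report the marginal mean ratio from the chosen model.
- Apply the same rule to the secondary count outcomes.

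The cost is a short change of text in the protocol or analysis plan, with no new data and no change to the sample size. The downside is slightly lower efficiency if another family of models fits better.

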## Introduction

Unhealthy alcohol use is a leading cause of morbidity and mortality among young people, including among university students in whom unhealthy alcohol use is associated with academic impairment, damage to self and others, and institutional costs [45]. In Switzerland and worldwide, a significant proportion of the mortality among young people is attributed to alcohol [13, 35, 36]. Students frequently experience the consequences of unhealthy alcohol use and the consequences tend to increase over time, despite prevention efforts [27]. Students are therefore an appropriate target for secondary prevention interventions aiming at reducing unhealthy alcohol use [1].

**Table 1 Tab1:** Schedule of enrollment, intervention and assessment (SPIRIT flow diagram)

Smartphone-based secondary prevention intervention for students with unhealthy alcohol use: study protocol of a parallel group randomized controlled trial					
Study periods	Inclusion procedure	Baseline assessment	Follow up		
Time point (month)	0	0	3	6	12
Expected duration (minutes)	3	10	10	10	10
Inclusion criteria	x				
Patient Information and informed consent	x				
Demographics (questionnaire)	x	x			
Primary outcome variables (questionnaires)		x	x	x	x
Secondary outcome variables (questionnaires)		x	x	x	x
Other outcomes of interest (questionnaires)		x	x	x	x
Randomization		x			
Intervention group		Access granted to application			
Application usage data		For intervention group participants, throughout follow-up period			

A challenge for addressing unhealthy alcohol use is that few with unhealthy alcohol use actively seek treatment [18]. Information technology has the potential to reach large parts of the general population [19, 22]. Compared to face-to-face interventions, interventions using information technology have a greater reach, can be more easily implemented, and are more consistent [42]. Numerous electronic interventions using CD-ROM, computers, or the Internet have been developed and tested [31, 50]. Electronic screening and brief intervention are considered effective methods for reducing unhealthy alcohol use [49, 56].

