### Study hypotheses

#### Main hypothesis

Participants randomized to receive access to a smartphone app targeting unhealthy alcohol use will have greater reductions in drinking 6 months later, compared to participants who did not receive access to the app.

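### The primary model does not adjust for baseline drinking, so its 6-month contrast is less precise than the planned data allow

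*Protocol article*

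**What the plan says.** The section Statistical analyses in the protocol article defines the primary analysis as a between-arm comparison of weekly drinks at month 6. If a negative binomial distribution fits, the model is as follows.

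- Random part: "The model will specify subject and recruitment site as random effects".
- Fixed part: "intervention and time as fixed effects (with a time * intervention interaction term".
- Covariates: "The model will be adjusted for age and gender".

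No term for baseline drinking is listed, and nothing restricts the arms to the same baseline mean.

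The measure is available. The schedule in Table 1 marks the primary outcome at months 0, 3, 6 and 12 ("Primary outcome variables (questionnaires) x x x x"). Under Recruitment procedure, only people who complete the baseline questionnaire enter the trial, and randomisation follows it.

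The aim is worded in two ways. Under Main hypothesis, participants given the app "will have greater reductions in drinking 6 months later". Under Statistical analyses, the alternative is that they "will report a smaller volume of drinking at the 6-month follow up".

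**The concern.** Drinking measured before randomisation with the same instrument is normally a far stronger predictor of drinking at 6 months than age or gender. The model as listed can treat it in only two ways. If the baseline visit is an outcome row, the 6-month interaction is a difference in change, which carries the baseline noise of both arms. If baseline is left out, the 6-month comparison ignores it.

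Precision on the primary endpoint is at stake. A secondary matter is clarity. With a time-by-intervention term in the model, the coefficient that answers the 6-month question depends on which visits are rows and how time is coded. The two wordings of the hypothesis point to different coefficients.

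**Working it through.** **The plan's own figure.** Sample size starts from 551 per group for 90% power at a 5% type I error. With the stated intraclass correlation of 0.001, 551 × [1 + (400 − 1) × 0.001] = 770.8, or 771. The cluster size of 400 is inferred because it returns the stated figure; the article does not give it. Then 771 × 0.10 = 77.1, 771 + 77 = 848, and 2 × 848 = 1696. The chain reproduces. The 551 itself cannot be rebuilt, because no effect size, standard deviation or dispersion is given. The article also does not say whether it assumed a level or a change comparison.

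**Inputs for the comparison.** Model terms and covariates come from Statistical analyses, visits from Table 1, and 1:1 allocation from the Abstract. The correlation r between baseline and 6-month drinking is not in the documents, so it is assumed to lie between 0.3 and 0.7. The calculation is a linear approximation to the count model, with equal variance σ² at each visit and complete data.

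**Formulas, with n per arm.**

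- Unadjusted 6-month difference: variance 2σ²/n.
- Difference in change: each person's change has variance 2σ²(1 − r), so the contrast is 2(1 − r) times the unadjusted one.
- Baseline-adjusted difference: residual variance is σ²(1 − r²), so the contrast is (1 − r²) times the unadjusted one.
- Change relative to adjusted: 2(1 − r)/(1 − r²) = 2/(1 + r).
- Unadjusted relative to adjusted: 1/(1 − r²).

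**Results.**

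| r | Change / unadjusted | Adjusted / unadjusted | Change / adjusted | Unadjusted / adjusted |
|---|---|---|---|---|
| 0.3 | 1.40 | 0.91 | 1.54 | 1.10 |
| 0.5 | 1.00 | 0.75 | 1.33 | 1.33 |
| 0.7 | 0.60 | 0.51 | 1.18 | 1.96 |

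The change contrast has the larger variance of the two unimproved options only when 2(1 − r) > 1, that is, when r < 0.5.

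**Does the subject random effect already do the adjusting?** No. Generalised least squares under a random intercept with categorical time gives these variances for the 6-month contrast, relative to the unadjusted one, at r = 0.3, 0.5 and 0.7:

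- follow-up rows only: 1.00 at each r;
- baseline rows kept, 6-month level (main effect plus interaction): 1.00 at each r;
- baseline rows kept, interaction only: 1.40, 1.00 and 0.60;
- baseline rows kept, arms constrained to one baseline mean: 0.91, 0.75 and 0.51.

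Only the constrained form reaches the precision of covariate adjustment, and the article does not specify it.

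**In participants.** Suppose 551 per group gives 90% power for an unadjusted comparison. Then the same power needs 502, 414 or 282 per group with baseline adjustment, and 772, 551 or 331 with the change contrast, at r = 0.3, 0.5 and 0.7.

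**The case against.** The strongest defence is that this is a choice between accepted analyses. The arms are randomised, so every 6-month contrast above keeps its type I error and is free of bias. That stands: the loss is in precision only.

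The defence can add that the article promises to use all available data and schedules the outcome at baseline, so baseline is probably an outcome row and the interaction is the test. If so, and if r is high, the loss is modest: 1.18 at r = 0.7. This also stands, although the loss is not zero at any r below 1.

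Visit rows, time coding and the exact contrast are commonly left to a statistical analysis plan, so their absence here is not itself a fault. The covariate list is different, because the article states it outright.

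A reader might infer more than the text supports:

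- *That the two hypotheses contradict each other.* With randomised arms the expected baseline difference is zero, so in a linear model a greater reduction and a lower 6-month level have the same expectation. The wording needs aligning, but the aims do not conflict.
- *That the trial loses a definite amount of power.* Any absolute figure needs a mean, dispersion and rate ratio that the article does not give. Take 551 per group as giving 90% power unadjusted, with a two-sided 5% test and no clustering penalty. Then 848 × 0.9 = 763 per group gives 96.8% unadjusted. At r = 0.3 it gives 89.7% for change and 97.9% baseline-adjusted.
- *That the choice of count distribution is part of the fault.* The negative binomial is named as the expected model and selection is described as a matter of fit. That is a separate question, commonly left to the analysis plan.

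**Conclusion.** The point holds as a matter of precision. The stated primary model adjusts only for age and gender, and no 6-month contrast it yields reaches the precision that the planned baseline measure allows. For r between 0.3 and 0.7, the variance is 1.54 to 1.18 times the baseline-adjusted variance if change is tested, and 1.10 to 1.96 times if the unadjusted level is tested. These figures rest on the assumed range of r, equal variances, complete data and a linear approximation. The direction holds for any r between 0 and 1.

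It would be wrong to conclude that the primary analysis is invalid or biased, or that 1696 participants is the wrong number. Neither follows. This should be fixed, as a free improvement, and it is not a defect that undermines the trial.

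**What to change.** In Statistical analyses, model the 3-, 6- and 12-month outcomes with baseline drinks per week as a covariate (for example log(baseline + 1)), visit as a categorical factor, and intervention by visit. Keep age, gender and the random effects as stated. Alternatively, keep baseline in the outcome vector and constrain the arms to a common baseline mean.

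Name the 6-month intervention/control rate ratio as the single primary contrast. Reword the Main hypothesis so that it refers to the 6-month level, as the alternative hypothesis in Statistical analyses does.

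The cost is a few sentences in the analysis plan. Baseline drinking is already scheduled for every participant, so no assessment or participant is added. The change should be recorded before outcome data are compared by arm.
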